## Abstract

**Background:**

Chronic carotid artery occlusive disease is associated with a high risk of ischemic events and long-term neurological deficits. Optimising surgical revascularisation outcomes requires an integrated understanding of anatomical, hemodynamic, and functional factors. This study aims to assess the neuro-radiological, clinical, and cognitive outcomes following cerebral revascularisation in patients with chronic internal carotid artery occlusion.

**Methods:**

This single-centre, prospective, open-label interventional longitudinal study includes 60 patients with chronic internal carotid artery occlusion undergoing superficial temporal artery-to-middle cerebral artery (STA–MCA) bypass at National Centre for Neurosurgery in Kazakhstan. The primary endpoint of the study is the incidence of ischemic stroke during the 6-month follow-up period after surgery. Pre- and postoperative evaluations include detailed angiographic assessment of collateral circulation and donor vessel diameter, as well as cerebral perfusion imaging using arterial spin labelling MRI. Neurological and cognitive function are assessed using standardized clinical and neuropsychological tests. Early and six-month follow-up evaluations focus on bypass patency, perfusion changes, and clinical outcomes.

**Discussion:**

By integrating anatomical, hemodynamic, and functional data, this study aims to identify predictors of successful revascularisation and favorable clinical outcomes. Correlation of postoperative angiographic and perfusion findings with cognitive and neurological recovery may refine surgical decision-making, enhance risk stratification, and optimize individualized patient care. Ultimately, this comprehensive approach seeks to improve the overall efficacy and safety of STA-MCA bypass in patients with chronic carotid artery occlusive disease.

**Trial registration:**

ClinicalTrials.gov NCT07396025. Registered on February 5, 2026.

## Introduction

Cerebrovascular diseases remain a major global health challenge because of their substantial clinical, societal, and economic burden. According to the Global Burden of Disease 2021 study, stroke is the second leading cause of mortality among non-communicable diseases worldwide and the third leading cause of death and disability combined, accounting for nearly 7 million deaths annually In 2021, approximately 93.8 million individuals were living with the consequences of stroke, while 11.9 million new stroke events were reported globally [1]. Ischemic stroke accounted for approximately 65.3% of all stroke cases [2], with large vessel occlusion implicated in up to 46% of ischemic events [3].

A major challenge in chronic carotid artery occlusive disease is identifying patients most likely to benefit from surgical revascularization while optimizing treatment strategies and understanding postoperative neurological and cognitive outcomes. The role of extracranial–intracranial (EC -IC) bypass remains controversial. The Carotid Occlusion Surgery Study (COSS) reported no reduction in recurrent ischemic stroke despite improved cerebral hemodynamics following bypass [4,5]. Conversely, the Japanese EC -IC Bypass Trial (JET) and JET-2 study suggested potential benefits of revascularization in carefully selected patients with documented hemodynamic compromise [6,7]. Subsequent observational studies have reported similar findings in selected high-risk populations [8,9]. These inconsistent results highlight the need for further investigation into postoperative hemodynamic, neurological, and cognitive outcomes to improve patient selection and surgical decision-making.

Key factors influencing long-term outcomes after direct EC-IC bypass include graft patency, stroke incidence, and functional recovery [10]. These outcomes are determined by the precision of the surgical technique, baseline and postoperative hemodynamic characteristics, and the extent of cerebral revascularisation achieved. However, there is a limited amount of high-quality longitudinal evidence evaluating the relationship between postoperative collateral flow development and long-term neurological and cognitive recovery. In particular, whether improvements in cerebral hemodynamics translate into meaningful functional and neurocognitive benefits remains insufficiently characterized. This knowledge gap limits the ability to optimize patient selection and refine prognostic assessment after revascularization, providing an important rationale for the present study.

Although emergency EC-IC bypass for acute strokes has demonstrated positive neurological outcomes [11,12], its effect on long-term neurological recovery in patients with chronic steno-occlusive cerebrovascular disease has not been sufficiently investigated. In patients with chronic internal carotid artery (ICA) occlusion and documented cerebral hypoperfusion, the long-term neurological and cognitive effects of superficial temporal artery–to–middle cerebral artery (STA-MCA) bypass remain insufficiently characterized. Existing studies evaluating postoperative cognitive outcomes after EC-IC bypass are limited by small sample sizes, heterogeneous methodologies, and incomplete longitudinal follow-up [13–15]. Furthermore, the relationship between postoperative cerebral perfusion improvement and neurological or cognitive recovery has not been systematically investigated. This evidence gap limits understanding of the functional consequences of revascularization and highlights the need for prospective studies evaluating hemodynamic, neurological, and cognitive outcomes following STA-MCA bypass in this high-risk population.

To address these knowledge gaps, this prospective single-arm interventional cohort study aims to evaluate hemodynamic, neurological, and cognitive outcomes following STA-MCA bypass in patients with chronic ICA occlusion and documented cerebral hypoperfusion. The primary endpoint is the incidence of recurrent ischemic cerebrovascular events, defined as ischemic stroke or transient ischemic attack occurring within 6 months after surgery. The secondary endpoints include postoperative neurological and cognitive improvement, assessed using standardized neurological and neuropsychological measures, and their relationship with changes in cerebral perfusion assessed using arterial spin labeling magnetic resonance imaging and angiographic parameters of revascularization. Specifically, the study aims to investigate whether postoperative hemodynamic improvement correlates with neurological recovery and cognitive trajectories following revascularization. By integrating radiological, perfusional, and functional assessments, this study seeks to improve prognostic evaluation and refine patient selection for surgical revascularization in chronic carotid artery occlusive disease.

### Study objectives

#### Primary objective.

To evaluate the incidence of ischemic stroke during the 6-month follow-up period after surgery.

#### Secondary objective.

To assess early postoperative haemodynamic changes, graft patency, changes in neurological and cognitive outcomes at 6 months, all-cause mortality at 6 months, perioperative complications, and the extent of cerebral revascularisation on follow-up imaging.

## Methods and analysis

### Study design

This study is a prospective, single-arm, single-centre, interventional cohort study according to the 2025 SPIRIT (Standard Protocol Items: Recommendations for Interventional Trials) Statement (S1 Appendix) and SPIRIT (Fig 1).

**Fig 1 pone.0354103.g001:**
[figure not shown]
Participant timeline: Schedule of enrollment, interventions, and assessments. Abbreviations: Preop – preoperatively, PostOp0 – Immediately postoperatively, PostOp6–6 months postoperatively, UV – Unscheduled Visit.

### Study population, settings and eligibility criteria

#### Study Population.

Patients with chronic ICA occlusion who underwent elective STA-MCA bypass surgery were enrolled between July 2025 and December 2027.

#### Study setting.

This single-centre study was conducted at the Department of Vascular and Functional Neurosurgery of the National Centre for Neurosurgery, a tertiary referral institution located in the capital city that provides neurosurgical care to the entire national population. With a capacity of 160 beds, the Centre represents the only specialized neurosurgical facility of its kind in Kazakhstan and serves as a regional referral hub for neighboring Central Asian countries [16].

#### Patient selection.

The study requires a multidisciplinary team comprising a neurologist, neurosurgeon, neuropsychologist, neuroradiologist, biostatistician, and research administrator.

Patients will be identified through the Department of Vascular and Functional Neurosurgery. STA-MCA bypass procedures for patients with chronic ICA occlusion will be performed by a team of neurosurgeons within the department. Neurosurgeons must have experience in vascular anastomosis and have successfully conducted STA-MCA bypass surgery on at least 10 patients. Neurological and cognitive assessments will be conducted by a consultant neurologist and neuropsychologist. All radiological imaging will be independently reviewed and interpreted by two radiologists from the Department of Radiology.

Baseline symptomatic status will be incorporated as an adjustment variable in multivariable and longitudinal analyses to account for differences in baseline risk and recovery potential. Exploratory subgroup analyses by symptom status will be performed where sample size permits.

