## Study procedure and intervention

### Clinical and radiological assessments

#### Radiological assessment.

The assessment schedule is given in Table 1. To evaluate the ICA occlusion, a three-level assessment will be conducted using CTA of the head and neck vessels, MRI ASL and Time-of-flight (TOF) sequences, and a confirmatory assessment of occlusion during DSA. All imaging studies will be performed and interpreted by neuroradiologists and neurosurgeons, with findings reviewed collaboratively.

**Table 1 pone.0354103.t001:** Data collection schedule.

Assessments	Preop	PostOp0	PostOp6	UV

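### No masking of the mRS, NIHSS and cognitive raters to postoperative perfusion is specified, although correlating perfusion change with those scores is the study's specific aim

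*Protocol article*

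**What the plan says.** The abstract's Methods paragraph sets the frame: "This single-centre, prospective, open-label interventional longitudinal study includes 60 patients". Under Patient selection, "Neurological and cognitive assessments will be conducted by a consultant neurologist and neuropsychologist". The next sentence of that section deals with the images: "All radiological imaging will be independently reviewed and interpreted by two radiologists from the Department of Radiology". Independence is thus specified for reading images, and nothing comparable is specified for clinical scoring.

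The last paragraph of the Introduction states the aim: "Specifically, the study aims to investigate whether postoperative hemodynamic improvement correlates with neurological recovery and cognitive trajectories following revascularization". The Discussion repeats it.

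On timing, Postoperative study procedures places CTA at 1–3 days and ASL MRI at 3–5 days after surgery, and repeats the neurological and cognitive tests before discharge. Follow-up assessment puts CTA, MR perfusion and all the scores into one six-month assessment without an order.

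The nearest thing to a separation of data is in Neurological assessment, which has preoperative and six-month results recorded separately before they enter the common database. Limitations links the open-label design to generalisability and selection bias. For cognitive testing it names learning effects, mood, fatigue and education. A rater's knowledge of the imaging is not mentioned.

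**The concern.** In a single-arm surgical study nobody can be masked to the operation, but a rater can be masked to the imaging result. In the correlation of interest, perfusion change is the explanatory variable, and change in mRS, NIHSS or cognition is the outcome. A rater who knows that a patient's perfusion improved may score that patient a little more favourably, and one who knows it did not may do the opposite. That error follows the explanatory variable, so it produces association where none exists or enlarges one that does. The mixed models and covariate adjustment under Statistical analysis do not remove it, because no covariate measures rater expectation.

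With no control group, this within-cohort association is a main basis for what the article hopes to say about prognosis and patient selection.

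**Working it through.** **1. The plan's own figure.** Sample size calculation gives 52 evaluable patients for a paired comparison: two-sided α 0.05, 80% power, standardised effect 0.40, within-subject correlation ρ = 0.5. The effect on the difference scale is 0.40/√(2(1 − ρ)) = 0.40/√1 = 0.40. The noncentral t distribution then gives n = 52 (power 80.8%), and 86.2% at n = 60. At n = 60, ρ = 0.3 gives 73.1% and ρ = 0.7 gives 97.6%. All stated figures reproduce. They concern a pre-post change, not the correlation, and masking alters none of them. I use 52 and 60 below only as the numbers of patients.

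**2. Could a rater know the result before scoring?**

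| Question | What the article says |
|---|---|
| Who scores? | Neurologist and neuropsychologist, no masking condition (Patient selection) |
| Who reads images? | Two radiologists, independently (Patient selection) |
| Order before discharge | CTA days 1–3, ASL days 3–5, scoring before discharge; same stay, no rule on release of results |
| Order at six months | One assessment, no order fixed |
| Separate recording | Concerns data entry, not what a rater knows |

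Nothing in the text prevents it, and nothing says that it happens.

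**3. Which measures are exposed?** mRS and NIHSS require judgement and are the most exposed. Cognitive function assessment describes a standardised battery (MoCA, RAVLT, Kohs blocks, Stroop) with standardised administration, and with alternative versions and norms where available, so it is less exposed. On the imaging side, perfusion change is the main variable. Early patency may vary little, because a non-functioning bypass is an exclusion criterion. Patency at six months can still vary.

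**4. Illustration of size.** The bias *b* is assumed; no document gives it. Let the true correlation be 0, and let the rater shift the change score by *b* SD per SD of perfusion change. Then

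- induced correlation: r = b/√(1 + b²);
- Fisher z: k = atanh(r) × √(n − 3);
- false-positive rate: Φ(k − 1.96) + Φ(−k − 1.96).

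For b = 0.2 and n = 52: r = 0.2/√1.04 = 0.196, k = 0.199 × 7 = 1.39, and the rate is Φ(−0.57) + Φ(−3.35) = 0.285.

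| Assumed b | Induced r | False positives, n = 52 | False positives, n = 60 |
|---|---|---|---|
| 0 (masked) | 0 | 5% | 5% |
| 0.1 | 0.10 | 11% | 12% |
| 0.2 | 0.20 | 29% | 32% |
| 0.3 | 0.29 | 54% | 61% |

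The induced r is close to *b* by construction. The table shows how sensitive a test of this size would be to such a bias. It does not estimate the bias in this trial.

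**The case against.** A reader might infer that the raters do see the images. The documents do not support that. "Open-label" concerns treatment, and no sentence says that the neurologist or neuropsychologist receives ASL or CTA results. Nor does Radiological assessment show it. It reads "All imaging studies will be performed and interpreted by neuroradiologists and neurosurgeons, with findings reviewed collaboratively", which names neither rater and follows an account of how the occlusion is established. If anything, it supports the view that scoring and image reading are separate roles.

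It can also be argued that the order of procedures within a visit belongs in the full protocol, which is not shown. That has some force for operational detail. It has less force for whether raters are masked at all, since the article does describe independent image reading and several sources of error in cognitive testing.

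Other points against a heavier weighting stand:

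- The illustration rests wholly on assumed shifts. It treats scores as continuous although mRS and NIHSS are discrete, and the article does not name a particular correlation test.
- Quantitative perfusion mapping and separate recording limit contamination to some degree, though neither is masking.
- The association is not among the listed outcome definitions. The regressions are called exploratory, and Limitations asks for associative interpretation and external validation.
- The ischaemic stroke outcome requires imaging confirmation of suspected events and is outside this point.

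**Conclusion.** The point holds in a limited form. No masking of the clinical and cognitive raters to postoperative perfusion, or to six-month patency, is specified, and the schedule allows them to know the results before scoring. The planned correlation is therefore open to expectation bias, chiefly for mRS and NIHSS. The direction would be towards the association the study hopes to find. The size is unknown, and the 11% to 54% range at n = 52 depends entirely on the assumed *b* of 0.1 to 0.3.

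The affected analysis is secondary and exploratory. The change is still worth making, because the bias acts directly on the stated specific aim, analysis cannot remove it afterwards, and prevention is cheap. Enrolment is planned to December 2027, so an amendment could still protect later assessments.

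**What to change.** State in Patient selection, Postoperative study procedures and Follow-up assessment that:

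- at discharge and at six months the neurologist and neuropsychologist complete and lock mRS, NIHSS and the cognitive battery before seeing ASL or CTA results. For the six-month scores the wording should also cover the early postoperative results, since a rater who has been given them is already partly unmasked;
- the radiologists quantify CBF and asymmetry without access to the clinical and cognitive scores;
- where care, or confirmation of a suspected stroke under Definitions of outcomes, requires a rater to see imaging sooner, this is recorded as unmasked, and the correlation is repeated without those assessments as a sensitivity analysis. Both results should be shown, because the excluded patients are unlikely to be typical.

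**Cost.** An order-of-procedures statement and one extra data field, with no change to sample size or visits. "The study requires a multidisciplinary team comprising a neurologist, neurosurgeon, neuropsychologist, neuroradiologist, biostatistician, and research administrator", so scorer and image reader are already separate roles. The downside is later release of imaging to these raters, longer if the early results are withheld until the six-month scoring. That no extra staff is needed assumes that the scoring neurologist is not managing the patient from the scans, which the article does not say. If that is not so, a different rater would be needed for mRS and NIHSS, or the limitation should be stated.

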### Eligibility criteria

#### Inclusion.

Chronic ICA occlusion confirmed by computed tomography angiography (CTA), magnetic resonance angiography (MRA), and digital subtraction angiography (DSA).Evidence of cerebral hypoperfusion on magnetic resonance imaging (MRI) arterial spin labelling (ASL) within the territory of the occluded ICA, defined as a ≥ 30% reduction compared with the contralateral hemisphere.Modified Rankin Scale (mRS) score of 0–3 at baseline.Preserved language comprehension, with no more than mild motor aphasia and no significant cognitive impairment.Adults aged 18–80 years.Provision of written informed consent by the patient or a legally authorised representative.Willingness and ability to comply with follow-up assessments.

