#### Exclusion.

Large territorial infarction or marked cerebral atrophy on MRI.Bilateral ICA occlusion or concomitant neurovascular disease (e.g., cerebral aneurysm or arteriovenous malformation).Severe systemic comorbidities, life expectancy <2 years, or a mRS score >3.Cardiac conditions that are associated with a high risk of cerebral embolism (e.g., prosthetic heart valves, infective endocarditis, intracardiac thrombus, sick sinus syndrome, cardiac myxoma, or cardiomyopathy with left ventricular ejection fraction <25%; atrial fibrillation, patent foramen ovale, and atrial septal aneurysm are not exclusion criteria).Contraindications to MRI, CTA, DSA, iodinated contrast agents, or required perioperative antiplatelet therapy.Non-functioning STA-MCA bypass.Participation in another interventional or experimental study within the previous 12 months, including those involving ionizing radiation.Pregnancy.

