**Hemodynamic parameters**				
Collateral circulation patterns	+			
Location and length of the internal carotid artery occlusion	+			
Circle of Willis configuration	+			
ASL perfusion metrics	+	+	+	
Cerebral blood flow (CBF) asymmetrical indices	+	+	+	
Infarct burden	+	+	+	
White matter hyperintensities	+			
Bypass patency and the diameter of STA		+	+	+

Abbreviations: Preop – preoperatively, PostOp0 – Immediately postoperatively, PostOp6–6 months postoperatively, UV – Unscheduled Visit, TIA – transient ischemic attack, BMI – Body mass index.

Included patients will undergo CTA of the head and neck vessels with a slice thickness of 0.5-0.625 mm to confirm ICA occlusion and to measure the diameter of the donor STA branch at 2 mm distal to its bifurcation.

MRI perfusion studies will be conducted before surgery on 1.5 or 3 Tesla MRI to evaluate cerebral blood flow (CBF) and determine the extent of cerebrovascular insufficiency. The main perfusion method will be ASL, which will provide quantitative CBF values, assess the degree of perfusion deficit, and reveal signs of compensatory collateral circulation based on the presence of arterial transit artifacts (ATA). Imaging parameters are described in in S1 Table.

DSA will be performed using a biplane digital subtraction angiography system (Artis Zee, Siemens) with a 6F guiding catheter at a frame rate of 7.5 frames per second. The angiographic assessment will evaluate the presence of communicating arteries, the completeness of the Circle of Willis, and the extent of collateral circulation. Hemodynamic compensation will be quantified by analyzing filling times and phase delays across the arterial, parenchymal, and venous phases, expressed in frames. Image analysis will be conducted using Siemens Artis Q angiography software to ensure accurate and reproducible measurements.

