#### Definitions of outcomes.

The primary outcome is defined as the incidence of ischemic stroke during the 6-month follow-up period after surgery. This outcome will be assessed based on clinical evaluation and confirmed by neuroimaging (MRI or CT) in cases of suspected new neurological deficits, in accordance with standard diagnostic criteria for ischemic stroke.

Secondary outcomes included early postoperative haemodynamic change (≤7 days) assessed using the same imaging modality; graft patency was defined as uninterrupted flow through the bypass on intraoperative ICG and postoperative CTA; changes in cerebral haemodynamic status from baseline to 6 months after surgery will be assessed using ASL MRI and defined as a quantitative increase in regional CBF in the affected hemisphere and/or a reduction in interhemispheric perfusion asymmetry compared with baseline; change in neurological status from baseline to 6 months assessed using the NIHSS and the mRS; changes in cognitive function from baseline to 6 months based on standardised neuropsychological testing; all-cause mortality at 6 months; perioperative complications within 30 days (including intracranial haemorrhage, hyperperfusion syndrome, seizures, wound complications, and graft occlusion); and angiographic extent of revascularisation on follow-up imaging.

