### Statistical analysis

Continuous variables will be reported as mean with standard deviation or median with interquartile range, depending on distribution. Categorical variables will be presented as frequencies and percentages. The primary outcome, change in cerebral hemodynamic status from baseline to 6 months, will be analyzed using a paired t-test or Wilcoxon signed-rank test, depending on data distribution. Mean change in CBF and/or perfusion asymmetry will be reported with 95% confidence intervals.

Early postoperative and 6-month changes in neurological and cognitive scores will be analyzed using paired tests. Categorical outcomes, including graft patency, recurrent TIA or stroke, complications, and mortality, will be reported as proportions with 95% confidence intervals.

Where appropriate, exploratory regression analyses will be performed to identify factors associated with hemodynamic improvement and clinical outcomes. Potential predictors may include age, sex, baseline perfusion deficit, vascular risk factors, duration of symptoms, and preoperative neurological status. Given the limited sample size, multivariable models will be restricted to a small number of clinically relevant covariates.

Because repeated measurements will be obtained from the same participants, analyses will account for within-subject correlation. Continuous repeated outcomes will be analysed using linear mixed-effects models, with time point entered as a fixed effect and participant ID as a random intercept. This approach allows estimation of postoperative change while accounting for correlation between repeated measures within individuals and accommodating incomplete follow-up data under a missing-at-random assumption.

A p-value <0.05 will be considered statistically significant. All analysis will be performed using Stata 19.5.

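### The haemodynamic outcome can be met by a fall in flow on the untreated side, because reduced asymmetry counts on its own and the measure to be reported is left open

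*Protocol article*

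**What the plan says.** Three parts of the protocol article bear on this point.

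- **Inclusion.** Hypoperfusion on ASL in the territory of the occluded ICA is "defined as a ≥ 30% reduction compared with the contralateral hemisphere". The opposite hemisphere is the reference, and no absolute CBF level is set.
- **Definitions of outcomes.** The 6-month change in haemodynamic status, listed among the secondary outcomes, is "defined as a quantitative increase in regional CBF in the affected hemisphere and/or a reduction in interhemispheric perfusion asymmetry compared with baseline".
- **Statistical analysis.** The change is tested with a paired t-test or a Wilcoxon signed-rank test, and "Mean change in CBF and/or perfusion asymmetry will be reported with 95% confidence intervals".

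On the data: the Radiological assessment section names ASL as the main perfusion method, "which will provide quantitative CBF values, assess the degree of perfusion deficit". Table 1 lists ASL perfusion metrics and CBF asymmetry indices as separate rows, both at the preoperative, early postoperative and 6-month visits. CTA is scheduled at the same visits. Contralateral ICA stenosis is not listed as an item in Table 1. The Exclusion section rules out "Bilateral ICA occlusion or concomitant neurovascular disease (e.g., cerebral aneurysm or arteriovenous malformation"; contralateral stenosis is not mentioned there.

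**The concern.** With *and/or* as the connector, either limb of the definition is enough. The second limb, "a reduction in interhemispheric perfusion asymmetry compared with baseline", is not a measure of the operated side alone. It improves when affected-side flow rises, and it also improves when contralateral flow falls. Progression of contralateral disease, or any other loss of flow on that side, would then satisfy a definition that is meant to describe the effect of the bypass.

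The repeated *and/or* in Statistical analysis adds a second weakness. The estimate may be CBF change, asymmetry change or both, and nothing fixes the choice before the data are seen, so the more favourable measure could be the one reported.

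This matters because the Introduction asks whether haemodynamic improvement goes with neurological and cognitive recovery, and the analysis section plans exploratory regressions on haemodynamic improvement. If improvement can come from the untreated hemisphere, those associations lose their meaning. The study has a single arm, so no comparison group would expose the problem.

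**Working it through.** **Figures in the plan.** The documents give no CBF value, no expected asymmetry change and no frequency of contralateral stenosis, so there is no stated figure to reproduce on this point. The sample size for the paired comparison does reproduce. With a standardised difference of 0.40/√(2(1−ρ)) and the noncentral t distribution, ρ = 0.5 gives n = 52 (power 80.8%), and 60 patients give 86.2%. At ρ = 0.3 and 0.7, 60 patients give 73.1% and 97.6%. These match the article, and the present point does not alter them.

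**When does asymmetry fall?** Let I be affected-side CBF and C contralateral CBF, with 0 for baseline and 1 for 6 months. Define A = 1 − I/C. Then

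A₁ < A₀ exactly when I₁/I₀ > C₁/C₀.

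Asymmetry therefore falls whenever the affected side does proportionally better than the other side. The affected side need not rise. If C drops by 10%, any loss of less than 10% on the affected side still lowers A.

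**Illustration.** All CBF values are assumed, in ml/100 g/min. The last column repeats the check with the symmetric index 2(C − I)/(C + I), because the article does not define the asymmetry index.

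| Case | I₀ → I₁ | C₀ → C₁ | 1 − I/C | 2(C − I)/(C + I) |
|---|---|---|---|---|
| a. Contralateral fall only | 32 → 32 | 48 → 42 | 33% → 24% | 40% → 27% |
| b. Contralateral fall only | 35 → 35 | 50 → 45 | 30% → 22% | 35% → 25% |
| c. Contralateral fall only | 35 → 35 | 50 → 40 | 30% → 12.5% | 35% → 13% |
| d. Loss on both sides | 35 → 33 | 50 → 45 | 30% → 27% | 35% → 31% |
| e. True gain on the operated side | 35 → 40 | 50 → 50 | 30% → 20% | 35% → 22% |

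For case a: 1 − 32/48 = 0.333 and 1 − 32/42 = 0.238.

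Cases a to d all meet the asymmetry limb, although the operated side gains nothing and in case d loses flow (2/35 = 5.7%). Cases b and e look almost alike on asymmetry (22% against 20% at follow-up), yet only e is a gain. Affected-side CBF separates them at once: a change of 0 against +5.

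The choice of index does not matter. Both versions fall in every row.

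**The case against.** **The wording is loose but the analysis may be sound.** No responder or success analysis is stated. The plan analyses continuous change, and both measures are collected at each scheduled visit, so an analyst could separate operated-side gain from contralateral loss. To move a cohort mean, contralateral decline within six months would have to be common or large, and nothing in the documents shows that it is. This stands as a limit on size. It does not remove the defect, because the stated definition still accepts asymmetry alone and the reported measure stays a free choice.

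**Absolute CBF has its own weakness.** Scans may be at 1.5 or 3 Tesla. If a visit scales all values by k, asymmetry is unchanged (1 − kI/kC = 1 − I/C), while absolute CBF change is not protected. This stands, and it is the reason to keep asymmetry as a supportive measure.

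**Flow drawn across from the other side** would raise affected-side CBF too, so an affected-side rule would not screen it out. This is correct. Only reporting each hemisphere separately makes such a shift visible.

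Three stronger readings are tempting, and the documents do not support them.

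- *The entry rule lets in the wrong patients.* A lowered contralateral reference makes entry stricter. If contralateral flow is 20% below normal, the affected side must be 1 − 0.70 × 0.80 = 44% below normal to show 30% asymmetry. Patients with low flow on both sides may be missed, but no one without a deficit is admitted by this route. Nor is bilateral occlusion the only relevant exclusion: the neurovascular disease clause is an open list, and whether it covers stenosis is unclear.
- *An old infarct alone brings patients over 30%.* This assumes a mean over the whole territory and tissue CBF values that the article does not give. Large territorial infarction is excluded, and imaging parameters are left to a supplementary table that is not shown.
- *The primary endpoint is compromised.* Statistical analysis does call the haemodynamic change primary, while the objectives and outcome definitions name ischaemic stroke. That is a separate contradiction and adds no weight here.

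**Conclusion.** The point holds for the outcome definition and the reporting rule. As written, a contralateral fall in flow is enough to meet the 6-month haemodynamic outcome, and the plan does not fix which of two measures carries the result. The first follows from the algebra of a ratio and does not depend on contralateral stenosis being present at baseline. The second follows from the wording alone.

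The size is unknown. The shift from 33% to 24% shows what the definition permits under assumed values; it does not estimate what will happen in this cohort. The point does not show that the cohort is misclassified at entry, that the 30% threshold is wrong or that the sample size needs to change. It is a wording defect that should be corrected, and correcting it is cheap.

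**What to change.** 1. In Definitions of outcomes and in Statistical analysis, remove *and/or*. Name the change in affected-hemisphere regional CBF from baseline to 6 months as the defining measure.
2. Always report three results together, each with its 95% confidence interval: affected-side CBF change, contralateral CBF change and asymmetry change, the last as supportive.
3. State that a fall in asymmetry is not called improvement when affected-side CBF has not risen.
4. Record contralateral ICA stenosis grade from the CTA already done at baseline and 6 months, and any contralateral revascularisation during follow-up. Repeat the haemodynamic analysis without patients who have significant contralateral stenosis or contralateral revascularisation, with the meaning of significant fixed beforehand. Part of this selection occurs after baseline, so it serves as a sensitivity analysis only.
5. Record field strength for each patient's scans, because absolute ASL CBF is more exposed to scanner differences than a within-scan ratio.

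Leave the entry criterion as it is. Enrolment is stated to have begun in July 2025, and changing eligibility now would create a new problem.

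Cost: two reworded passages, a few fields read from existing imaging and records, and a somewhat smaller sample in the sensitivity analysis. The Ethics section says that outcome measures have remained unchanged, so the clarification should be dated, recorded as a change and made before the 6-month perfusion results are examined.
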